### Secondary outcomes

6.3

The secondary outcomes include:•Length of stay, defined as the number of hours spent at the PACU.•Number of times administration of antidote Naloxone was necessary.•Consumption of opioid rescue medication measured upon arrival at the orthopaedic ward and after 6, 24, and 72 h postoperatively.•Opioid-related side effects, including post-operative nausea and vomiting (PONV), measured upon arrival at the orthopaedic ward and after 6 and 24 h postoperatively.•Postoperative pain will be measured using VRS upon arrival at the orthopaedic ward and after 6, 24, and 72 h postoperatively.

The primary and secondary outcomes will be measured by trained healthcare personnel at the orthopaedic department and recorded in RedCap (Research electronic data Capture). In addition, [name] will note the starting dose and whether the patient experienced toxicity in the dose-escalation program.

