#### Inclusion criteria

5.2.1

•Patients presenting with a hip fracture in the emergency department (collum femoris fractures, pertrochanteric fractures and subtrochanteric fractures. ICD-10-codes: DS720-722)•Age *≥* 60 years•Patients must be able to reliably assess their pain level using the Verbal Rating Scale (VRS) and be able to ask for supplementary analgesics as needed•Patients must be able to read and speak Danish and understand the information and be able to give informed consent

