### Baseline variables

6.1

For safety and reproducibility purposes, the baseline variables presented in Table 1 will be noted for each given methadone dose in the trial (see Table 2).

**Table 2 tbl2:** Secondary analysis.

Secondary analysis					
Variable	Level			Coef (95%CI)	p-value
Length of stay Pain	0.10 mg/kg 0.15 mg/kg 0.20 mg/kg 0.10 mg/kg 0.15 mg/kg 0.20 mg/kg			Ref. Ref.	n.a n.a
Variable	Level			IRR (95%CI)	p-value
Consumption	0.10 mg/kg	at	6 h	Ref.	
	0.15 mg/kg	at	6 h		
	0.20 mg/kg	at	6 h		
	0.10 mg/kg	at	24 h	Ref.	
	0.15 mg/kg	at	24 h		
	0.20 mg/kg	at	24 h		
	0.10 mg/kg	at	72 h	Ref.	
	0.15 mg/kg	at	72 h		
	0.20 mg/kg	at	72 h		
Respiratory depression	0.10 mg/kg			Ref.	n.a
	0.15 mg/kg				
	0.20 mg/kg				
Variable	Level			OR (95%CI)	p-value
Side effects	0.10 mg/kg	at	6 h	Ref.	
	0.15 mg/kg	at	6 h		
	0.20 mg/kg	at	6 h		
	0.10 mg/kg	at	24 h	Ref.	
	0.15 mg/kg	at	24 h		
	0.20 mg/kg	at	24 h		
	0.10 mg/kg	at	72 h	Ref.	
	0.15 mg/kg	at	72 h		
	0.20 mg/kg	at	72 h		

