### Primary outcome

6.2

The primary outcome is the incidence of respiratory depression during the first 24 h after surgery. Respiratory depression is defined as a respiratory frequency below 10 breaths pr. minute and peripheral oxygen saturation below 94 % despite 4 ltr/min oxygen and will be registered upon arrival at the orthopaedic ward and again 6 and 24 h after surgery.

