### Secondary analysis

7.3

The analysis of the secondary outcomes will consist of:•Survival analysis focusing on the length of stay at the PACU. Kaplan Meier curves will be presented and pseudo-observations together with linear regression will be used to assess if the length of stay at the PACU differs between the three dose levels [17]. If the fit of the linear regression is not satisfactory, then bootstrapped confidence intervals and p-values will be presented instead of their parametric counterparts.•Poisson regression will be used to investigate whether the number of times administration of Naloxone was necessary is dependent on the given dose level. The model control will be a graphical assessment of the deviance residuals. If the model control yields an unsatisfactory fit a negative binomial regression will be used instead.•In relation to postoperative opioid consumption generalized estimating equations will be used as the variability is partially determined by the hospitals infrastructure, which is not reproducible. The p-value will be based on the contrast as time can be a potential effect modifier of the exposure. If convergence issues regarding the maximum likelihood estimate are present then a Poisson or negative binomial regression with clustered standard errors will be performed instead, depending on the distribution of the deviance residuals.•Presence of opioid-related side-effects will be analysed by way of generalized estimating equations with a logit link function, as the variability is connected to the given hospital and therefore not reproducible. The p-value will be based on the contrast as time can be a potential effect modifier of the exposure. If convergence issues regarding the maximum likelihood estimate is present then a logistic regression with clustered standard errors will performed instead.

Postoperative pain will be analysed by way of a mixed effect model with bootstrapped confidence intervals, as the outcome is a Likert scale and the variability is fully determined by the given and is thus reproducible in other settings. The p-value will be based on the contrast as time can be a potential effect modifier of the exposure.

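### Pain and side effects are compared across CRM-assigned dose groups, but the SAP's baseline table and models contain no pre-dose pain or symptom score

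*SAP article*

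**What the plan says.** **Timing.** Section 6.4 has methadone given intravenously when anaesthesia starts. Section 6.3 then lists the readings. For pain: "Postoperative pain will be measured using VRS upon arrival at the orthopaedic ward and after 6, 24, and 72 h postoperatively". For opioid-related side effects, including nausea and vomiting: "measured upon arrival at the orthopaedic ward and after 6 and 24 h postoperatively". Every listed reading of both outcomes follows the dose and the operation.

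**Baseline.** Section 6.1 states that "the baseline variables presented in Table 1 will be noted for each given methadone dose in the trial". Table 1 (section 5.3) lists fracture type, age, sex, ASA class, BMI, tobacco, alcohol, chronic opioid use and 15 comorbidities. It has no pain score and no symptom.

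**Models.** Section 7.3 states: "Postoperative pain will be analysed by way of a mixed effect model with bootstrapped confidence intervals". The presence of side effects goes into a GEE with a logit link. Both p-values rest on a contrast that lets time modify the dose effect. Neither description includes a pre-dose value of the outcome.

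**Allocation and adjustment.** Under section 6.4 the CRM assigns the dose from the primary outcomes of earlier patients. The end of section 7.3 foresees adjustment for strong predictors, which it does not name, when the difference between doses is judged clinically insignificant.

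**Feasibility.** The inclusion criteria (section 5.2.1) say: "Patients must be able to reliably assess their pain level using the Verbal Rating Scale (VRS". The VRS is therefore usable at entry.

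**The concern.** Without randomisation, nothing balances the dose groups at entry. CRM allocation is also sequential, so dose can track calendar time. A group that happens to arrive with more pain or more symptoms will then look like a dose effect, in either direction.

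The SAP's own text makes such differences plausible. Section 1.1 describes these fractures as markedly painful even without movement. It also lists constipation, nausea, itch, dry mouth, vertigo and sedation as common opioid effects. Table 1 has a row for chronic opioid users, and section 5.2.2 excludes addiction but not chronic use. Such a patient may have several of these symptoms before the study injection, yet the GEE models presence, not onset.

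What is at stake is the secondary objective in section 4, which asks how the doses are tolerated with regard to side effects, together with the pain comparison. A pre-dose value that nobody recorded cannot be recovered after dosing.

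**Working it through.** The SAP gives no figure on this point to reproduce. The first step is a reading of the schedule; the rest is illustration on stated assumptions.

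**1. Schedule**

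| Outcome | First reading (6.3) | Pre-dose value in Table 1 | Baseline term in model (7.3) |
|---|---|---|---|
| Pain (VRS) | ward arrival | none | none |
| Side effects | ward arrival | none | none |

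The ward-arrival reading cannot serve as baseline, because the dose may already have changed it. A patient-level random effect accounts for correlation among a patient's post-dose readings, but it does not remove a difference between groups that existed before dosing.

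**2. Conditional adjustment.** The rule in section 7.3 adjusts when a difference looks clinically unimportant. When a difference looks important, which is when confounding would mislead, no adjustment is planned. Nor does the rule supply a variable that is outside the planned baseline set.

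**3. Pain: possible imbalance.** Input: at most 40 patients (section 7.4). Assumptions: an even split, 40/3 ≈ 13 per dose, or an uneven pair of 5 and 30, which a CRM can produce; pre/post correlation r = 0.3 to 0.6.

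- SE of a chance baseline difference, in SD units: √(1/n₁ + 1/n₂). For 13 and 13, √(2/13) = 0.39. For 5 and 30, √(1/5 + 1/30) = 0.48.
- Shift in the unadjusted pain contrast from a one-SE imbalance: r × SE. Even split: 0.3 × 0.392 = 0.12 to 0.6 × 0.392 = 0.24 SD. Uneven pair: 0.3 × 0.483 = 0.14 to 0.6 × 0.483 = 0.29 SD.

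**4. Pain: precision.** At a single time point, adjustment removes a share r² of the residual variance: 0.3² = 9% to 0.6² = 36%. At 13 per group, 80% power and two-sided 5%, the detectable difference is (1.960 + 0.842) × 0.392 = 1.10 SD unadjusted. Multiplying by √(1 − r²) gives 1.05 SD at r = 0.3 and 0.88 SD at r = 0.6.

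**5. Side effects.** Let p be the new-onset rate and b the pre-existing rate, assumed independent. Observed presence is 1 − (1 − p)(1 − b). The SAP gives no side-effect rates, so p = 0.10 and 0.20 for two doses is an assumption.

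| b in both groups | Observed rates | Odds ratio |
|---|---|---|
| 0 | 0.100, 0.200 | (0.200/0.800)/(0.100/0.900) = 2.25 |
| 0.02 | 0.118, 0.216 | (0.216/0.784)/(0.118/0.882) = 2.06 |
| 0.05 | 0.145, 0.240 | (0.240/0.760)/(0.145/0.855) = 1.86 |
| 0.10 | 0.190, 0.280 | (0.280/0.720)/(0.190/0.810) = 1.66 |

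A common background raises both rates and pulls the odds ratio towards 1. An unequal background confounds. With p = 0.10 at both doses, and b = 0.02 in one group and 0.10 in the other, the odds ratio is (0.190/0.810)/(0.118/0.882) = 1.75 without any dose effect.

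**The case against.** The strongest reply is that this is a condensed SAP article. Table 1 is a reporting table, and vital signs and pain scores at admission are commonly left to the protocol. That stands. A reader might infer that the trial takes no pre-dose reading at all; the article shows only that none is in its baseline table or models. Those two items do belong to an SAP, so that narrower statement is a fair finding.

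Three further inferences are tempting but unsupported.

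- **That the primary outcome is compromised**, for instance by patients whose usual saturation is low. Section 6.2 requires "a respiratory frequency below 10 breaths pr. minute and peripheral oxygen saturation below 94 % despite 4 ltr/min oxygen". Both parts must hold, so a low usual saturation alone is not an event, and nothing suggests that patients enter with so low a respiratory rate. The MTD uses this outcome only.
- **That existing complaints are held against methadone as such.** All three groups receive it and Table 2 contrasts doses. The harm is confounded or diluted contrasts and inflated absolute rates, with no systematic direction between doses.
- **That the groups are compared with no baseline information.** Table 1 compares many characteristics by dose, including chronic opioid use, with tests (section 7.1). What is missing is the baseline of the outcome itself.

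It can also be said that postoperative pain and postoperative nausea are postoperative by definition, that pain from an unfixed fracture may predict later pain poorly, and that these are secondary outcomes without multiplicity control (section 7.5). The first does not remove confounding by the entry state. The second is why r is shown as a range. The third limits the weight of the point.

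**Conclusion.** The point holds for pain and side effects only. The SAP compares non-randomised dose groups on both without a pre-dose score in Table 1 or a baseline term in either model, and its conditional adjustment rule does not close the gap.

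The size depends on assumptions. For r between 0.3 and 0.6, adjustment would remove about 9% to 36% of the residual variance of a single-time-point pain contrast, and a one-SE chance imbalance would shift the unadjusted contrast by roughly 0.12 to 0.29 SD. The gain in the planned multi-time-point mixed model may differ. The variance share should not be converted into patients saved out of 40, because that number was set for CRM accuracy (section 7.4) and not for a pain contrast.

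The primary outcome and the MTD are not materially affected. This is a cheap improvement to stated secondary outcomes, not a flaw in the trial's main result.

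**What to change.** 1. Record the VRS and the same side-effect checklist used later, once before dosing, at the inclusion contact. If the protocol already collects them, use those values.
2. Show both in Table 1 by dose group.
3. Include baseline VRS as a covariate in the pain mixed model in every case, separately from the conditional rule at the end of section 7.3.
4. Adjust the side-effect GEE for pre-dose presence of the symptom, or report side effects as new or worsened alongside simple presence.

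The cost is a few extra REDCap fields per patient, at a contact where REDCap and the case report form are already in use (section 6.4), and one covariate per model. For patients already dosed without such a reading, the value cannot be recreated, and the report should state this as a limit on the dose contrasts.

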### Exposure

6.4

The exposure is a categorical variable where the groups are defined as:•0.10 mg/kg methadone at the beginning of surgery.•0.15 mg/kg methadone at the beginning of surgery.•0.20 mg/kg methadone at the beginning of surgery.

When patients are included from the ED the orthopaedic doctor will contact the primary investigator [name], who will assign each patient to a methadone group (0,10 mg/kg, 0,15 mg/kg or 0,20 mg/kg) using the model-based Continual Reassessment Method (CRM). This method uses registered primary outcome from the previous included patients or the prespecified prior if no data has been collected (see Fig. 1). The assigned methadone group is registered into REDcap and will be used to estimate the individual dose of methadone, which is calculated by multiplying methadone group with patient weight. This individual methadone dose will be written on a case report file (CRF). The primary care provider from the ED is responsible for withdrawing study medicine and placing the syringe near the patient together with the CRF. The individual dose of methadone is administered intravenously by the certified registered nurse anaesthetist when anaesthesia is commenced. The CRF will follow the patient to the orthopaedic ward.

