### Primary analysis and treatment assignment

7.2

This trial uses the Bayesian continual reassessment method, therefore stopping guidelines and probabilistic priors in relation to toxicity MTD (maximal tolerable dose) need to be determined before inclusion of the first patient. The stopping rules for the trial include:•If 40 persons are included.•If the probability of the lowest dose exceeding a predetermined toxicity threshold (set at 0.10) is greater than 95 % and more than 10 persons are included.•If the 95 % credibility interval of the toxicity level for the MTD is between 0 and 0.10 (a clinically acceptable toxicity level) and more than 10 persons are included.•If all the above stopping rules are fulfilled and 10 participants are included.

The predetermined toxicity threshold for the lowest dose considers the assumption that toxicity increases with higher doses. Thus, if the toxicity at the lowest dose surpasses the clinically acceptable level of 0.10, further dose escalation should be avoided. The pre-specified prior to this analysis consists only of presumed toxicity levels of the different doses and the alpha parameter. The presumed toxicity levels for the three doses is set to 0.05, 0.1, and 0.2 for 0.10 mg/kg, 0.15 mg/kg, and 0.2 mg/kg, respectively, and alpha follows a *γ*(1*,* 1) distribution. After the specification of the prior and stopping rules, the method uses the dose-response curve to escalate or deescalate the doses in a non-conservative manner (see Fig. 2) and close arms if one or more stopping rules are met. The 1-parameter model estimates the MTD more efficiently by escalating through the doses faster [16]. This is acceptable because the risk of adverse events by respiratory depression is low. Furthermore, there may be difficulties fitting the model or obtaining consistent estimates of model parameters in a two-parameter model [16]. Thus, we choose to use the 1-parameter model for this study.

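### The secondary analyses compare three dose categories against 0.10 mg/kg, but the CRM will usually leave at least one group very small, and no stated fallback covers sparse groups or zero-event cells

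*SAP article*

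**What the plan says.** - Section 6.4 (Exposure): "The exposure is a categorical variable where the groups are defined as" 0.10, 0.15 and 0.20 mg/kg.
- Table 2 (section 6.1) lists "0.10 mg/kg 0.15 mg/kg 0.20 mg/kg 0.10 mg/kg 0.15 mg/kg 0.20 mg/kg" for length of stay and pain. It repeats the three levels for consumption, respiratory depression and side effects, always with 0.10 mg/kg as reference. Respiratory depression and consumption are reported as IRRs, side effects as ORs.
- Section 6.4, on allocation: "This method uses registered primary outcome from the previous included patients or the prespecified prior if no data has been collected". Section 7.2 adds that the method will "escalate or deescalate the doses in a non-conservative manner", with a cap of 40 patients and two rules that can stop the trial once more than 10 are included.
- Section 7.2, on the prior: "The presumed toxicity levels for the three doses is set to 0.05, 0.1, and 0.2 for 0.10 mg/kg, 0.15 mg/kg, and 0.2 mg/kg", with alpha following a gamma(1, 1) distribution in a one-parameter model.
- Section 7.3: naloxone is analysed by Poisson regression, with negative binomial if the fit is poor. For consumption, "In relation to postoperative opioid consumption generalized estimating equations will be used"; side effects use GEE with a logit link. The GEE fallback is a regression with clustered standard errors, used if the maximum likelihood estimate has convergence problems. Pain uses a mixed model with bootstrapped intervals. PACU stay has bootstrapped intervals as a fallback.

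**The concern.** A CRM gathers patients around the current MTD estimate; it is not built to fill three groups for comparison. Every fallback in section 7.3 is triggered by poor fit or non-convergence and keeps the same three categories. None addresses a group with a handful of patients or a cell without events.

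The secondary objective is tolerability by dose: side effects and rescue consumption. If the plan is applied literally, some Table 2 cells will have no finite estimate and some intervals will be too narrow. Choosing a new reference or model after seeing the allocation would be the data-driven analysis that section 8 says this SAP is meant to prevent.

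**Working it through.** **The plan's own figure.** Section 7.4 gives N = 40 for target 0.10, accuracy 0.6 and odds ratio 2. The cited formula is not printed, so 40 cannot be derived exactly. With odds 0.1/0.9 at the MTD and a factor of 2 per dose step, the three scenarios are 0.10/0.182/0.308, 0.053/0.10/0.182 and 0.027/0.053/0.10. Averaged over these, a nonparametric optimal benchmark selects correctly with probability 0.606 at N = 30 and 0.659 at N = 40. The simulated CRM gives 0.63–0.67 at 40. So 40 meets the stated accuracy and is not in dispute.

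**How the groups fill.** Inputs from section 7.2: presumed toxicities 0.05/0.10/0.20, gamma(1, 1), cap 40, both stopping rules after more than 10 patients, no escalation constraint. Assumed: one patient per cohort; power or one-parameter logistic form; plug-in or posterior-mean toxicity estimate.

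One step by hand (power form, plug-in). The prior picks 0.15 mg/kg. After one patient there without toxicity, with L = ln 10 = 2.303:

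E(alpha) = [1 − 1/(1+L)²] / [1 − 1/(1+L)] = 0.908/0.697 = 1.303.

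The estimates are 0.10^1.303 = 0.050 and 0.20^1.303 = 0.123. The second is nearer 0.10, so the next patient goes to 0.20 mg/kg, and the 0.10 group fills only after toxicities. With posterior means the prior estimates are 1/(1 + ln(1/p)) = 0.250, 0.303 and 0.383, so allocation begins at 0.10 mg/kg.

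Size of the 0.10 mg/kg group (1,500 to 4,000 runs per cell, model-chosen start):

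| True toxicity | Plug-in: P(empty) | Plug-in: P(≤5) | Posterior mean: P(≤5) | Posterior mean: median |
|---|---|---|---|---|
| Presumed 0.05/0.10/0.20 | 0.30–0.35 | 0.48–0.51 | 0.26–0.29 | 13–15 |
| MTD 0.20 mg/kg | 0.64–0.70 | 0.82–0.85 | 0.62–0.63 | 3 |
| Low, 0.01/0.02/0.04 | 0.85–0.90 | 0.95–0.97 | 0.85 | 3 |
| MTD 0.10 mg/kg | 0.04–0.06 | 0.11 | 0.04–0.05 | 31 |

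With posterior means the group is never empty. If the MTD is 0.10 mg/kg, the 0.20 group is the sparse one instead (2 or fewer patients in 0.51–0.78 of trials). The probability that all three groups have at least 5 is at most 0.24 in every cell; a repeat simulation gave at most about 0.18.

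**Rare outcomes.** If the reference rate is 5%, the chance of no event among n patients is 0.95^n: 0.77 at n = 5 and 0.51 at n = 13. Allowing for the random group size, there is no reference event (or no reference patient) in 0.61–0.74 of trials under the presumed toxicities (0.62–0.76 in the repeat) and 0.85–0.95 if the MTD is 0.20 mg/kg. With dose as categories, Poisson and negative binomial fits both set each group's mean to its observed mean. A zero mean gives an infinite log rate ratio whatever the dispersion, so changing the distribution does not help.

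**Consumption.** Assumed: overdispersed counts with mean 4, 25 patients in the comparison group, no true difference. Coverage of the nominal 95% robust interval is 0.70, 0.81, 0.88 and 0.92 for 2, 3, 5 and 10 reference patients, so the error is 1 − 0.81 = 19% at n = 3 and 1 − 0.88 = 12% at n = 5. With 3–4 reference patients rejection is 15–20%; a small-sample variance with a t reference brings it to about 4–5%. The degrees of freedom must reflect the small group. For 3 versus 25 the Satterthwaite-type value is (1/3 + 1/25)² / [(1/3)²/2 + (1/25)²/24] = 0.1394/0.0556 = 2.5, far below the number of patients minus parameters.

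**Side effects.** At an assumed risk of 30%, a reference cell with all or no events has probability 0.7^n + 0.3^n: 0.58, 0.37 and 0.17 at n = 2, 3 and 5. The simulated size of the binary GEE test was 5–8% over 300 data sets. The Monte Carlo range around 5% is ±1.96 × √(0.05 × 0.95/300), that is 2.5–7.5%, so this is close to nominal.

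**Trigger wording.** GEE solves estimating equations and maximises no likelihood, so there is no maximum likelihood estimate whose convergence can be checked.

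**The case against.** A reader might infer that the 0.10 mg/kg group will often be empty, that most Table 2 contrasts cannot be estimated, and that the secondary objective goes unanswered in most trials. The document does not support this. An empty reference depends on an estimator and starting dose that the article does not state; the flowchart and CRM-output figures, not readable here, may bear on it. With posterior means the group is never empty. If the MTD is 0.10 mg/kg, which the hypothesis allows, it is the largest group. Even with an empty reference, 0.15 versus 0.20 mg/kg can be estimated after re-referencing.

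The zero-event argument should not be stretched either. About four events (40 × 0.10) describes respiratory depression at the target rate. Section 1.1 names nausea among the common opioid side effects, so nothing implies four such events. The naloxone rate is not given, and naloxone is not in Table 2. Length of stay, pain and consumption contrasts are generally estimable when the groups are not empty.

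Nor are all the error bars wrong: pain has bootstrapped intervals and the binary GEE error is mild. The consumption figure rests on an overdispersion that the SAP does not give.

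Replacing the categories by one linear dose term everywhere is also debatable. The CRM models toxicity only. Section 1.1 reports a sharp difference in analgesic duration between 5–10 mg and 20 mg or more, which argues against assuming linearity for pain or consumption.

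Finally, section 7.5 says these are not the primary analyses. All of this narrows the point. What remains is that some group is nearly always small and the plan has no rule for it.

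**Conclusion.** The point holds in limited form. At least one dose group will usually be too small for the planned categorical contrasts: all three reach 5 patients in at most about a quarter of simulated trials. It is the 0.10 mg/kg group when toxicity is low or the MTD is 0.20 mg/kg, and the 0.20 mg/kg group when the MTD is 0.10 mg/kg.

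As written, the respiratory depression rate ratio against 0.10 mg/kg (and that for naloxone, if about as rare) has no reference event in about 60–75% of trials under the presumed toxicities. Uncorrected robust inference for consumption is too confident when a group has about 3–5 patients. The maximum likelihood trigger is a wording error that needs no simulation.

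The sizes rest on cohorts of one, the two model forms, the toxicity scenarios listed and the assumed outcome rates. The MTD estimate is not affected. The change should be made before the analysis, but it concerns secondary outcomes only.

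**What to change.** In section 7.3 and the Table 2 notes:

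1. Use a small-sample-corrected sandwich variance with a t or F reference, and degrees of freedom that reflect the smallest group, for all GEE and clustered models.
2. Use Firth-penalised or exact estimation for respiratory depression, naloxone and any side effect with an empty cell.
3. Reword the fallback trigger as non-convergence of the estimating equations.
4. State before analysis that contrasts involving a group below a preset size (for example 5) are shown descriptively, and that estimable contrasts such as 0.15 versus 0.20 mg/kg are reported after re-referencing.
5. Optionally add a linear dose trend as a supportive analysis with its monotone-linearity assumption stated. It should not replace the categories in every model.

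The cost is SAP wording and standard software options. Corrected intervals will be wider, and some comparisons will be descriptive only. The trend term gains precision at the price of its linearity assumption.
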